### Ethical considerations

Previous research does not indicate that IPS leads to an exacerbation of symptoms or has other negative clinical implications [10]. Entering competitive employment may, for some participants, be perceived as stressful. This will be addressed by close contact with participants, case managers, and employers to ensure adaptation of special requirements or sick leave if necessary. All adverse events (e.g., hospitalization, increase in symptoms, decrease in functioning, and incidents of suicide) will be registered and reported. All safety measures can be seen in Table 4.

Information about the trial is presented to all potential participants both verbally and in written form so they can make an informed decision about their participation before signing written consent. It will be clearly explained that participation is voluntary and that withdrawal can occur at any time without consequence for treatment possibilities. Decisions regarding participation will not influence clinical care in any way.

The trial protocol has been reviewed by the Ethics Committee in the Capital Region of Denmark (registration #H-3-2012FSP34), although they waived the need for ethical approval because it is not a biomedical trial. Furthermore, the trial has been reported to the Danish Data Protection Agency (registration #01768 RHP-2012-011) and is registered at http://www.clinicaltrials.gov (#NCT01722344).

## Discussion

This is the first trial investigating the effects of IPS in Denmark and will be one of the largest randomized trials investigating IPS to date. As a comparison, 14 trials included in a Cochrane review showed a median sample size per arm of 70 participants and a range of between 20 and 156 [11]. Furthermore, this trial will be the first large-scale trial, with a long follow-up period, enhancing the IPS intervention with both cognitive remediation and social skills training. The design of the trial has several strengths. Firstly, a sample size calculation was made according to the primary outcome, hours in competitive employment or education. The power is estimated for all secondary outcome measures, showing that a sample size of 750 participants is sufficient to show a relevant effect size with a power above 80 %. Secondly, the risk of selection bias related to allocation sequence generation and concealment is limited, as the Copenhagen Trial Unit performs a central web-based randomization according to a computer-generated allocation sequence. Thirdly, assessors are blinded, and blinding will be used wherever possible to prevent bias. Data will be analyzed according to the intention-to-treat principle, which together with an intense follow-up of patients should limit the risk of attrition bias. Finally, internal validity is addressed by implementing fidelity ratings. The fidelity ratings have high priority and will be conducted throughout the trial period to ensure that evidence-based practice is adhered to.

The trial also has some limitations. Firstly, there is a risk of performance bias because participants and practitioners are not blinded. It could be argued that both participants and practitioners conducting the experimental intervention would be more enthusiastic and keen to perform well because of the novelty of participating in a research project. To account for this, blinding is employed in all other aspects of the trial. Secondly, the control condition is heterogeneous. Participants will receive different vocational interventions, which will vary by individual and depend on factors such as type of social benefit the individual is receiving. Policy decisions could change the conditions in the job centers during the trial period and this could affect vocational rehabilitation, a fact that may limit the generalizability of the control condition. Thirdly, recruitment procedures may affect the external validity of the trial. The staff at the mental health centers is responsible for recruitment and may not successfully identify all eligible participants. Finally, there are initiatives in the Danish IPS model that exclude the possibility of highest IPS fidelity score. For example, the employment specialists will use a percentage of their time on the authority work in the job centers instead of manualized IPS.

If the results of this trial show IPS to be effective compared with the control group, these positive results will support the preliminary evidence that the method is generalizable to a variety of sociodemographic contexts. Furthermore, if IPS supplemented with cognitive remediation and work-related social skills training shows that the effects can be further improved, it will bring important knowledge for further research on and implementation of IPS.

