Randomized clinical trials of IPS have been conducted in different socioeconomic and cultural contexts with different results. A review found that four of five trials with the lowest employment rates were non-US trials [7]. Furthermore, a randomized trial from the UK investigating IPS compared with service as usual did not show significant vocational effects [18]. The authors suggest that implementation of IPS in labor markets and economies where economic disincentives may lead to lower levels of motivation can be challenging [18]. Until now, IPS trials have not been conducted in Denmark, where barriers to implementation and replication of previous international findings may exist. Firstly, Denmark is characterized by complex employment legislation and a highly specialized labor market with a high minimum wage and few entry-level jobs, which could impact both the implementation of IPS and potential effect sizes. Secondly, the social security system is generous compared with those of other countries, and this may be a perceived or real financial disincentive for returning to competitive employment and hence influence motivation levels [18, 19].

Thus, it is crucial to investigate whether IPS can be implemented in Denmark, and a large-scale trial with low risk of bias and a long follow-up period is needed. The present trial will be the largest randomized clinical trial to date to investigate the effects of IPS and IPS enhanced with cognitive remediation and work-related social skills training. The primary outcome is number of hours in competitive employment or education at 18-month follow-up.

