### Control group

#### Group 3 – service as usual

Participants allocated to the control group will receive “service as usual” only. This consists of participants continuing to receive OPUS or community mental health treatment. Also, it involves individual case management and medical review, referral to external vocational agencies, and involvement in group programs which may involve participation in vocationally oriented groups. The psychiatric treatment provided will be the same in all three groups throughout the trial period with the one exception that controls do not get the integrated IPS intervention. In general, the participants allocated to the control group are to have close mandatory contact with the local vocational authority (job centers), depending on what kind of benefits they receive. Hence, the participants in the control group will receive a variety of vocational rehabilitation support at the job centers in accordance with the train and place principle.

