Explorative outcomes	Register-based	Hours in competitive employment or education in follow-up period			X
	Register-based	Competitive employment or education at some point during follow-up period			X
	Register-based	Days to first employment or beginning of education			X
	Register-based	Days in employment or education		X	X
	Register-based	Average monthly earnings		X	X
	Register-based	Hours of work per week among those who obtain competitive employment		X	X
	Register-based	Long-term sick leave		X	X
	Register-based	Social benefits	X	X	X
	Obtained through interview	Function measured with Global Assessment of Functioning (GAF) [39]	X	X	
	Obtained through interview	Health-related quality of life measured with 12-Item Short Form Health Survey (SF-12) [40]	X	X	
	Self-reported questionnaire	Recovery measured with Mental Health and Recovery Measure (MHRM) [41]		X	
	Self-reported questionnaire	Empowerment measured with Empowerment Scale [42]	X	X	
	Self-reported questionnaires	Satisfaction with treatment. Measured with Client Satisfaction Questionnaire (CSQ) [43]		X	
	Register-based	Use of mental health services	X	X	X
	Obtained through interview	Substance abuse measured with Alcohol Use Disorders Identification Test (AUDIT) [44]	X	X	
	Self-reported questionnaire	Health-related quality-of-life measured with EQ 5D(EuroQOL five dimensions questionnaire) [45]	X	X

**Table 4 Tab4:** Safety measures and data collection

Outcome measure	Source of collection	Assessment	Baseline	18-month follow-up	30 + 60-month register follow-up
Safety measures	Obtained through interview	Psychotic and negative symptoms measured with Scale for the Assessment of Positive Symptoms (SAPS) and Scale for the Assessment of Negative Symptoms (SANS)	X	X	
	Obtained through interview	Depressive symptoms measured with Hamilton Depression Scale [36] (HAM-D6)	X	X	
	Obtained through interview	Suicidal ideation and actions. Measured with European Parasuicide Study Interview Schedule (EPSIS)	X	X	
	Death cause register, Civil Registration System (CPR)	Deaths (all causes)	X	X	X
	Hospital records	Number and length of hospital admissions both somatic and psychiatric		X	X
	Hospital records	Use of outpatient services	X	X	X

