### Sample size and power calculation

No previous IPS trials or similar studies have been conducted in Denmark that could contribute to an estimation of the expected average number of hours of work among participants in the IPS intervention. A European IPS multicenter trial found a difference between the IPS group and the control group (vocational services) of 150 h in competitive employment in an 18-month follow-up period, and standard deviation was 500 [19]. A difference of 150 h in competitive employment or education is considered clinically relevant. If the outcome within each intervention group is normally distributed with a standard deviation on 500 and with a true mean difference of 150 between the intervention and the control group, the present trial will need 250 participants in both intervention arms and additionally 250 control participants to be able to reject the null hypothesis that the population means of the experimental and control groups are equal with probability (power) of 80 %. The type I error probability associated with the null hypothesis is 1.25 %. A type I error of 1.25 % was chosen to give the possibility to make four comparisons: (1) IPS versus service as usual, (2) IPS versus IPS enhanced, (3) IPS enhanced versus service as usual, and (4) IPS + IPS enhanced versus service as usual. If we encounter difficulties in recruiting 250 participants to each group, we will exclude comparison (4) as a primary comparison. With three primary comparisons, we use a type I error of 1.67 % in the sample size calculation, accumulating a sample size of 236 patients in each group. Power calculations on calculations of the secondary outcome measures were carried out (Table 5) and indicate that a sample size of 250 patients per group would be adequate to detect relevant significant differences.

**Table 5 Tab5:** Power calculation

Outcome measure	δ expected difference in mean	σ expected standard deviation	α	Power	Reference
Days to first employment or beginning of education	68	45	0.0125	1.000 (*t* test)	Bond et al. [8] (2008),
Cognitive function	0.3	0.7	0.0125	0.989 (*t* test)	McGurk et al. [13] (2005)
The Brief Assessment of Cognition in Schizophrenia [32]					
Function measured with Personal and Social Performance (PSP) scale [31]	7	14	0.0125	0.999 (*t* test)	Kawata et al. [31] (2008). Nasrallah et al. [46] (2008) (No IPS studies use PSP scale. δ is estimated)

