### Data analysis plan

The main null hypothesis to be tested is that there is no difference between the three groups in hours in competitive employment or education in the 18-month follow-up period. All randomized participants will be analyzed, including those who stop receiving treatment, according to the intention-to-treat principle. All continuous outcome measures, including the primary outcome “hours in competitive employment or education”, will be analyzed by using generalized linear models. In situations in which the continuous measure is non-normally distributed, a non-parametric model will be used. Multiple imputations will be used to impute a distribution of missing values. Furthermore, linear mixed models with repeated measurements and unstructured covariance matrixes will be used to assess the potential interaction between time and intervention. The dichotomous secondary outcome “work or education at some point during the follow-up period” will be analyzed by using logistic regression. The secondary outcome “time-to-employment or education” will be analyzed by using the Cox proportional hazards model. All models will be adjusted for the stratification variables.

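### The stated adjustment set omits baseline type of social benefit, a register variable the trial already collects; prespecifying it in the hours model may add a little precision at almost no cost

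*Protocol article*

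**What the plan says.** On adjustment, the Data analysis plan states: "All models will be adjusted for the stratification variables". The Randomization section lists these as sex, work history (more or less than 2 months of competitive employment in the last 5 years), work readiness (match 2 or 3) and site.

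Benefit type appears in three other places in the Protocol article:

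- Group 3 – service as usual: the control participants' mandatory contact with the job centres varies, "depending on what kind of benefits they receive".
- Discussion, limitations: the control condition is heterogeneous, and the vocational interventions received "depend on factors such as type of social benefit the individual is receiving".
- Table 3: "Social benefits" is a register-based exploratory measure, marked at baseline as well as at follow-up. The Outcome and assessments section says that the DREAM register covers the whole population and holds disability pension, social security, sickness benefits and education eligible for state grants.

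The sample size rests on a "standard deviation on 500 and with a true mean difference of 150 between the intervention and the control group", with 80% power and 250 per arm.

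**The concern.** Benefit status at baseline is fixed before randomisation, comes from a whole-population register and needs no new data collection. The protocol itself links it to the vocational service a participant is likely to meet. It is also plausible, though the documents do not state it, that a person on disability pension, one on sickness benefit and one on a state education grant start at different distances from work or study, which is what the primary outcome counts. The existing stratifiers are coarse: two are two-level splits of work history and readiness.

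If benefit type explains variation in hours that the stratifiers do not, that variation stays in the error term of every primary contrast. The matter at stake is efficiency only. Randomisation protects the validity of the comparison with or without the covariate.

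**Working it through.** **Inputs from the Sample size section.** Difference 150 h; SD 500 h; power 80%; 250 per arm. On alpha: "The type I error probability associated with the null hypothesis is 1.25" per cent for four comparisons. For the fallback: "With three primary comparisons, we use a type I error of 1.67" per cent, with 236 per group. Sidedness is not stated.

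**Input not in the documents.** R² is the share of the residual variance in hours that benefit type explains beyond the stratifiers. It is assumed here, from 0 to 0.10.

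**Step 1: reproduce the plan's sample size.** n per arm = 2 (z₁₋α/₂ + z₀.₈₀)² (SD/δ)².

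- α = 0.0125, two-sided: 2 × (2.498 + 0.842)² × (500/150)² gives 248, against 250 stated.
- α = 0.05/3, two-sided: 2 × (2.394 + 0.842)² × (500/150)² gives 233, against 236 stated.
- One-sided tests would give 212 and 196, which do not match. The plan is therefore read as two-sided.

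Power at 250 per arm: SE = 500 × √(2/250) = 44.72 h; 150/44.72 = 3.354; 3.354 − 2.498 = 0.856; Φ(0.856) = 80.4%. The noncentral t gives 80.1%. The plan's figures are reproduced.

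**Step 2: add the covariate.** In a linear mean model with 500 h taken as the SD left after the stratifiers, the covariate changes the SD to 500 × √(1 − R²). Power = Φ(3.354/√(1 − R²) − 2.498).

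| Assumed extra R² | Residual SD (h) | δ/SE | Power, 250 per arm | n per arm for 80% | SE relative to no covariate |
|---|---|---|---|---|---|
| 0 | 500.0 | 3.354 | 80.4% | 248 | 1.000 |
| 0.01 | 497.5 | 3.371 | 80.9% | 246 | 0.995 |
| 0.02 | 495.0 | 3.388 | 81.3% | 243 | 0.990 |
| 0.05 | 487.3 | 3.441 | 82.7% | 236 | 0.975 |
| 0.10 | 474.3 | 3.536 | 85.0% | 224 | 0.949 |

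At R² of 0.01 to 0.02 the gain is 0.5 to 0.9 points of power. At 0.10 it is 4.6 points (85.0 − 80.4), and 24 fewer participants per arm (248 − 224) would be needed for 80%.

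**The case against.** The strongest case against is that nothing here is wrong. Adjusting for the stratification variables is standard practice and contradicts nothing. The sentence does not say that only those variables may be used, and a full analysis plan, not shown, may add others. That stands, and it is why this is a suggestion for efficiency and not a defect.

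The gain is also assumed. Work history and match category are already in the model and may overlap heavily with benefit type, so an extra R² near zero is possible. That stands too. Moreover, 500 h is an outcome SD from an earlier trial, not a residual SD. If the stratifiers already explain variance, power before any further covariate exceeds 80.4%, so it would be too strong to say that the design has no margin. Comparison (4), with 500 against 250, has about 91.5% power for the same difference.

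A reader might infer three stronger claims, and the documents do not support them:

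- That the protocol says benefit type shapes a participant's motivation. The Background remark, "this may be a perceived or real financial disincentive for returning to competitive employment", concerns the generosity of the Danish system compared with other countries, not differences between participants.
- That the covariate would resolve the limitation about a heterogeneous control condition. That limitation concerns what controls receive, possible policy change and generalisability. A main-effect covariate only absorbs outcome variance. Nor is the heterogeneity ignored: the section on adherence plans to record controls' contacts and the duration and content of their rehabilitation. Those data arise after randomisation, so they describe the control condition but cannot replace a baseline covariate.
- That the same gain applies to the yes/no and time-to-event outcomes. Odds and hazard ratios are non-collapsible, so a prognostic covariate changes the effect being estimated and need not shrink its standard error.

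Finally, the Data analysis plan moves to an unspecified non-parametric model if hours are non-normal. The table in the working does not apply directly to that fallback.

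**Conclusion.** The point holds as a minor, optional improvement. The stated adjustment set leaves out a pre-randomisation register variable that the trial collects and that the protocol connects to job-centre contact and vocational support. The omission causes no bias and contradicts nothing in the article.

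The benefit is limited to possible precision in the primary hours contrasts, from nothing to about 4.6 points of power over the assumed R² range. That range rests on three assumptions: the R² values themselves, 500 h as the SD remaining after the stratifiers, and a linear mean model. The documents do not settle where in the range the true value lies.

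**What to change.** Before outcome data are opened, add baseline type of social benefit to the stratification variables as a prespecified covariate in the hours model. Take it from the register at the last record before randomisation, in a few fixed categories (for example disability pension, sickness benefit, other social security, state education grant, none), with a rule for merging sparse ones. State whether the covariate is kept if the non-parametric model is used.

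A table of the primary contrast by benefit category could be added, labelled as descriptive only.

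The cost is one line in the analysis plan and a few degrees of freedom out of 750 (four with the five categories above). No new data are needed. If the full analysis plan already includes this covariate, no change is needed.

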## Trial status

The trial was initiated in October 2012. As of January 2015, 480 patients had been randomly assigned.

## Abbreviations

CIRCuiTS: Computerised Interactive Remediation of Cognition - Training for Schizophrenia
DREAM: Danish Register for Evaluation of Marginalization
IPS: Individual Placement and Support
PSP: Personal and Social Performance (scale)
